### Pilot Stage

The Pilot Stage took place in a single LTCH from May to August 2023, starting with retrospective data collection (for the period February 2022 to January 2023), continuing with a transition phase where the QI strategies were brought online and concluding with a one-month intervention phase. The main output from the Pilot Stage was a process evaluation to gather exploratory and evaluative insights to validate study materials, check assumptions, identify gaps in the interventions and evaluate in-field processes. A series of semi-structured interviews with LTCH staff (n=3), a focus group with ECPs (n=2), voluntary online surveys (n=10) and direct observation of the materials deployed in the home informed the process evaluation. In addition to these targeted sources of information input from the frontline workers of the Local Implementation Team was valuable to ground and validate our analytical interpretations in a deeper understanding of the local context of the home ((34–36)).

Fewer ECPs participated in the focus group than anticipated and this was likely at least partially due to the necessary timing of the pilot during the summer months, especially as the regular touchpoint of the resident family and friends council was on hiatus. However, even these few responses provided a valuable level of nuance regarding ECPs’ perceptions of the educational materials and of UTI treatment best practices that helped to identify areas for consideration and improvement for the stepped-wedge trial.

### Retrospective data collection

Facility and demographic data will be collected along with proposed outcomes metrics for a retrospective one-year period to provide historical insight, contextualize these data with home demographics and serve as true baseline for comparison with intervention phase data. Participating LTCHs will be provided detailed data dictionaries and template data entry forms to ensure consistency.

### Control Phase

The Control Phase will last between two and five months, depending on cluster number (Table 1). During the Control Phase, usual care will be given to the LTCH residents, and minimum and additional data elements (such as the number of urine cultures ordered and catheter use) will be collected on a monthly basis, as necessary, to answer both the primary and exploratory research questions. The complete list of variables is provided in **Appendix B: Outcome metrics**.

### Transition Phase

During the one-month Transition Phase, the research team will liaise with each LTCH to coordinate education and delivery of the interventions. The goals of the Transition Phase are to 1) provide level-setting foundational AMS knowledge and practices to help standardize the intervention across participating LTCHs and 2) coordinate the implementation of the intervention. To further ensure alignment, the research team will offer to connect the medical leadership of each LTCH with a physician member of the study working group for an optional peer-to-peer conversation about the guidelines and their experience with implementation within their practice.

During this phase the research team will deliver brief education sessions for LTCH staff (nurses, physicians, non-regulated healthcare staff, pharmacists) about the overprescribing of antibiotics, a reminder of when it is and is not appropriate to test for and treat UTI in older adults ((37,38)) and practices that can contribute to this problem. These sessions will be delivered in-person or by webinar at the discretion of the LTCHs. A recording will be made available for new staff and those unable to attend the synchronous sessions.

### Intervention Phase

The Intervention Phase will consist of two primary strategies: 1) ECP education and 2) monthly feedback letters to LTCH staff about facility urine culture ordering.

**Essential care providers education:** Although educational components are common in AMS interventions within LTCHs ((14,18,38–46)), they typically target physicians and/or nurses. Fewer studies have provided education for ECPs ((11)), despite ECPs’ influence on testing and treatment decisions ((16,47–49)). We designed these educational resources to increase understanding of AMS and the harms of unnecessary antimicrobial use among ECPs, and to outline a positive advocacy role for ECPs in UTI management.

Drawing on lessons learned from the Pilot Stage, taking a multi-modal approach to ECP education will help reach a broader audience among this diverse target population. Brief education sessions will be delivered in-person by a LTCH staff trained by the research team and asynchronously by leveraging digital communications and in-home communications (e.g., UTI best practice posters in common areas). In-person and live virtual sessions will be offered monthly, with exact frequency to reflect each LTCH’s unique needs, and delivered within regularly occurring events (e.g., monthly LTCH town halls). Educational materials will also be distributed to ECPs through videos, posters, newsletters and physical handouts made available at the LTCH. We hypothesize that this intervention will reduce urine culture ordering and antibiotic prescribing by increasing ECPs’ knowledge about AMS and, therefore, decreasing caregiver expectations for these tests and treatments when not clinically indicated.

**Feedback letter:** This strategy consists of monthly feedback given to LTCH staff (i.e., nurses, non-regulated healthcare staff, pharmacists, physicians) that shows the rate of urine cultures ordered by their facility in the past month relative to their previous data (retrospective, Control, Transition and previous Intervention Phase when relevant). Audit and feedback on antibiotic prescription use have been embraced for use with physicians ((50)). Feedback to nurses and non-regulated healthcare staff, however, has not been used as an intervention strategy in LTCHs, yet these professionals play particularly important roles in LTCHs. They collaborate with physicians in making these decisions typically by assessing the resident and communicating their observations to the physician and, in some cases, collecting a urine sample before the physician has assessed the resident ((49,51-53)). Comparing recent with past performance acts as a self-comparison, which can motivate recipients by establishing personal norms ((54)) and has been effective in other contexts ((55)). Feedback will also indicate the proportion of urine cultures aligned with best practice guidelines (for LTCHs able to collect signs and symptoms data), which is a more specific measure of stewardship than overall ordering rate alone ((56)). We hypothesize that the feedback strategy will increase institutional awareness and reduce perceived risk of negative outcomes of urine culture avoidance, ultimately leading to a decrease in urine cultures and antibiotic prescriptions.

Feedback will be provided to all LTCH staff (nurses, non-regulated healthcare staff, pharmacists, physicians) starting after the first month of the Intervention Phase, for a total of two to five cycles of feedback depending on the cluster number. The LTCH implementation team will work with the research team to identify appropriate medium(s) for this feedback (e.g., central communications location on the floor, email, bulletin boards, regular staff meetings). The feedback letter will also include reminders regarding urine culture ordering decision guidelines ((37,38)) and links to additional resources.

### Study measures

De-identified quantitative data will be collected monthly during the Control, Transition and Intervention Phases. Minimum data elements needed to answer the primary research questions include number of urine cultures ordered, antibiotic prescriptions for UTI, total antibiotic prescriptions and total days of residence. Additional data elements are necessary to answer the exploratory research questions and include signs and symptoms prompting urine culture orders, resident demographic characteristics, chronic conditions and functional status.

To contextualize the quantitative findings with the perspectives of the end users (LTCH staff and ECPs), we will additionally 1) conduct semi-structured interviews with 3–6 staff members from each LTCH after the Intervention Phase; 2) hold 2–3 focus groups with 4–6 ECPs each, within two months of the end of the intervention phase; and 3) collect qualitative data on perceptions and experience with the study through voluntary online questionnaires available to all LTCH staff and ECPs throughout the study. As with the Pilot Stage, qualitative data collection and validation will be supported by Local Implementation Teams.

### Data analysis

A series of descriptive (continuous variables) and frequency analyses (categorical variables) will be conducted to get a global sense of the sample responses.

Analysis will be done at the level of the LTCH as an intention-to-treat analysis. To evaluate research question 1, rate of urine culture (per 1,000 resident days) will be calculated for the retrospective data period. To evaluate research question 2a, a generalized linear mixed-effects model will be used to assess whether or not the intervention has an effect on the rate of urine culture (per 1,000 resident days). The model will include categorical, fixed effects for phase (control/intervention) and for each month to account for secular trends, as well as a random effects for LTCH. Data from the Transition Phase will be excluded from these analyses as we do not consider these data to be clearly Control or Intervention Phase data. To evaluate research questions 2b and 2c, a similar model will be used with the outcome measures rate of antibiotic prescriptions for UTI and total antibiotic prescriptions per 1,000 resident days. Exploratory analyses will use a similar model to evaluate the potential effect of the intervention on rate of urine cultures not aligned with guidelines. Alignment with guidelines will be estimated by comparing the signs and symptoms prompting each urine culture to meet the modified Loeb minimum criteria for UTI for a catheterized or non-catheterized resident ((37,38)).

Thematic analysis will be guided by ethnographic methods and Normalization Process Theory. Taking an iterative approach that draws on Grounded Theory ((35)), open-ended codes will be applied alongside selected evaluative codes developed from a Normalization Process Theory perspective ((57,58)). Ethnographic data reduction techniques will be applied to surface focused insights to support the overarching research questions for the study ((34,36,59)).

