## Methods

### Study overview

The study will be conducted in two stages. In the Pilot Stage, the protocol was implemented in a single LTCH for process evaluation (see **Appendix A: Protocol refinements**). The Trial Stage involves implementation in eight other LTCHs across Canada, with the main objective being an outcomes evaluation. The Trial Stage is designed as a stepped-wedge cluster randomized quality improvement study (**Table 1**) using a mixed-method approach. Quantitative data will evaluate the effectiveness of the protocol at reducing both testing and treatment for UTI, and qualitative data will contextualize the findings. Long-term care homes will be randomized to different starting times for the crossover from the control to intervention phases, with staff and residents blinded to their allocation sequence. Here, we present the final protocol, including changes informed by Pilot Stage findings. For a complete list of refinements made to the protocol following the Pilot Stage, refer to Appendix A: Protocol refinements.

**Table 1 t1:** Overview of the stepped-wedge design

LTCH	Cluster	Month 1	Month 2	Month 3	Month 4	Month 5	Month 6	Month 7	Month 8
a	1	C	C	T	I	I	I	I	I
b	1	C	C	T	I	I	I	I	I
c	2	C	C	C	T	I	I	I	I
d	2	C	C	C	T	I	I	I	I
e	2	C	C	C	T	I	I	I	I
f	3	C	C	C	C	T	I	I	I
g	4	C	C	C	C	C	T	I	I
h	4	C	C	C	C	C	T	I	I

Abbreviations: C, Control Phase (usual care is given); I, Intervention Phase (implementation of intervention); LTCH, long-term care home; T, Transition Phase (initiation of intervention)

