### Sample characteristics

A purposive sampling strategy was used to recruit large (approximately 200 residents) LTCHs across Canada. To be eligible, LTCHs had to provide long-term (permanent placement) residential care with 24-hour monitoring and medical assistance. Sample size calculations using Hemming and Taljaard’s approach ((30)) indicated that eight LTCHs across four clusters, observed for a total of eight months, would be sufficient to detect a clinically meaningful 20% reduction in rate of urine culture ordering (6.5 to 5.2 urine cultures per 1,000 resident days) at greater than 80% power and 5% significance level. The effect size is in line with previous studies that observed greater than 25% reduction in urine culture ordering ((31,32)) and is more conservative than 25% reduction used in sample size calculations for a similarly designed trial ((33)).

Two limitations of this trial are its smaller sample size and the purposive sampling technique, which will not provide a representative sample of LTCHs across Canada. However, this is the first pilot study of a novel intervention, so the smaller more homogenous sample will provide initial evidence on the effectiveness of the strategies, which will allow for improvement of the processes and materials.

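### Excluding the eight Transition home-months is unbiased but inefficient; keeping them as a third phase level gives a modest gain in precision from data already collected.

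*Protocol article*

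**What the plan says.** Table 1 ("Overview of the stepped-wedge design") gives every home one Transition month: homes a and b in Month 3; c, d and e in Month 4; f in Month 5; g and h in Month 6. The Study measures section confirms that these months are observed: "De-identified quantitative data will be collected monthly during the Control, Transition and Intervention Phases".

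For the rate of urine cultures, the Data analysis section specifies a generalized linear mixed model with a two-level phase effect (control or intervention), a categorical effect for each month and a random effect for home. It then states "Data from the Transition Phase will be excluded from these analyses", on the ground that Transition data cannot be clearly assigned to either phase. A similar model serves the two antibiotic outcomes and the exploratory outcome on guideline alignment.

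Sample characteristics describes "eight LTCHs across four clusters, observed for a total of eight months" as enough to detect a fall from 6.5 to 5.2 cultures per 1,000 resident days at "greater than 80% power and 5% significance level". It gives no intracluster correlation or between-home variance, and does not say whether the calculation allowed for the exclusion.

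**The concern.** The reason given supports keeping Transition months out of both the Control and the Intervention groups. A separate phase level does that, and also lets those months inform the month effects and home effects. Deleting them goes further than the reason requires.

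All the deleted cells lie in Months 3 to 6, the only months in which homes are in different phases. With a categorical month effect, the separation of intervention from secular trend depends largely on those months. The trial has eight homes, and the article itself names the small sample as a limitation. Because the same model form is reused, the loss recurs in each outcome.

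**Working it through.** **Step 1. Count Table 1** (homes in Control / Transition / Intervention).

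| Month | C | T | I |
|---|---|---|---|
| 1 | 8 | 0 | 0 |
| 2 | 8 | 0 | 0 |
| 3 | 6 | 2 | 0 |
| 4 | 3 | 3 | 2 |
| 5 | 2 | 1 | 5 |
| 6 | 0 | 2 | 6 |
| 7 | 0 | 0 | 8 |
| 8 | 0 | 0 | 8 |
| Total | 27 | 8 | 29 |

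The total is 27 + 8 + 29 = 64 home-months, of which 8 (one eighth) are dropped. Only Months 4 and 5 hold both Control and Intervention homes. That is true whether or not the Transition cells are kept.

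**Step 2. Inputs.**
- From the article: rates 6.5 and 5.2 per 1,000 resident days, so log(5.2/6.5) = log 0.8 = -0.223; about 200 residents per home; 5% significance; fixed month effects and random home effect.
- Assumed: two-sided test; 30.4-day months; Poisson counts; a Transition rate midway between the two (5.85); between-home SD of the log rate from 0 to 1.0.

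Resident-days per home-month are 200 × 30.4 = 6,080. Expected counts are 6.5 × 6.08 = 39.5 in Control, 5.2 × 6.08 = 31.6 in Intervention and 5.85 × 6.08 = 35.6 in Transition.

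**Step 3. Formula.** Each home-month's log rate has variance 1/(expected count), plus a variance shared within home. The generalised least squares variance of the phase effect is the matching diagonal element of (X'V⁻¹X)⁻¹. Power = Φ(0.223/SE − 1.96).

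**Step 4. The plan's own figure.** The stated power above 80% cannot be reproduced or refuted exactly, because no between-home variance is given. Under these assumptions and the planned model, power is 0.46 to 0.58.

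**Step 5. Transition dropped versus kept as a common third level.**

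| Between-home SD | SE, dropped | SE, third level | Change in variance | Power |
|---|---|---|---|---|
| 0 | 0.103 | 0.090 | -23% | 0.58 to 0.70 |
| 0.1 | 0.114 | 0.105 | -14% | 0.50 to 0.56 |
| 0.2 | 0.118 | 0.110 | -12% | 0.475 to 0.525 |
| 0.3 | 0.119 | 0.112 | -11% | 0.47 to 0.52 |
| 0.5 | 0.119 | 0.112 | -11% | 0.465 to 0.51 |
| 1.0 | 0.119 | 0.113 | -11% | 0.46 to 0.51 |

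Example at SD 0.3, with unrounded SEs 0.1186 and 0.1116: the variance ratio is (0.1116/0.1186)² = 0.886. Power is Φ(0.2231/0.1186 − 1.96) = Φ(−0.08) = 0.47 when dropped and Φ(0.2231/0.1116 − 1.96) = Φ(0.04) = 0.52 when kept.

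With home-by-month variation of SD 0.1 to 0.2 added (home SD 0.1 or 0.3), the variance falls 12 to 17%. With AR(1) decay of the within-home correlation and home SD 0.2 to 0.5, it falls 4 to 10%. Extra variation of either kind also lowers the starting power, so the gain in power points is then smaller.

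**Step 6. Where the gain comes from.** It comes from indirect links (Transition against Control in Month 3, Transition against Intervention in Month 6) and from better estimates of the month and home effects. At home SD 0.2 the Transition cells carry weights in the intervention estimate of about +0.089 for each cluster 1 home, +0.012 for each cluster 2 home, -0.045 for the cluster 3 home and -0.086 for each cluster 4 home.

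**Step 7. Sensitivity to the common-effect assumption.** The total weight is 2 × 0.089 = 0.178 on cluster 1 and 2 × (-0.086) = -0.172 on cluster 4. A 0.10 log-rate difference between their Transition effects therefore shifts the estimate by about 0.10 × 0.17 to 0.18, or about 0.02, against an SE of 0.11. At home SD 0.3, if Transition effects vary between homes and the model ignores this, the gain disappears at an SD of about 0.22. If variation of SD 0.2 is modelled as random, a gain of about 6% remains. If each home has its own fixed Transition effect, the estimate equals the exclusion result and the gain is zero.

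**The case against.** The strongest case against is that the exclusion is pre-specified, reasoned and unbiased, so this is a choice between two valid analyses. That stands: the point concerns efficiency and is neither an error nor a contradiction.

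A second objection is that the benefit rests wholly on a common Transition effect, which the article gives grounds to doubt. The Transition Phase section leaves the format of staff sessions to each home and makes the peer-to-peer conversation optional. Appendix A, change 3, widens that flexibility on purpose. This also stands in part, and the assumption is only approximate. But the planned model already assumes one intervention effect common to all homes. The variation needed to cancel the gain (SD about 0.22) is as large as the whole target effect (log 0.8 = -0.223).

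Three stronger readings are tempting, and the documents do not support them:
- *Deletion leaves only two concurrent months.* Table 1 has no month other than 4 and 5 with both phases, with or without the Transition data. The change adds none.
- *A third level leaves the contrast untouched.* The weights in Step 6 are not zero, so unequal Transition effects in early and late homes pass into the estimate.
- *The trial is shown to miss its stated power, and this change would repair it.* Without a stated between-home variance the first part cannot be settled. In none of the cases calculated does the change bring power to 80%.

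**Conclusion.** The point holds as a modest efficiency improvement. The stated reason justifies separating Transition months from both phases; it does not require discarding them. Under random home effects and Poisson counts, the common third level cuts the variance by about 11 to 14% at between-home SD 0.1 to 1.0. The 23% at SD 0 needs homes with no underlying difference in ordering rates and should be read as an upper limit. The corresponding gain in power is about 4 to 6 points, from roughly one half. Precision improved in every scenario tried with a common Transition effect.

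The size depends on the assumed variance components, about 200 residents per home and a roughly common Transition effect. The direction does not depend on the particular home SD, but it does depend on Transition effects not varying greatly between homes.

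**What to change.** In the Data analysis section, give the phase effect three levels (control, transition, intervention), keep the Transition home-months in the model, and report the intervention-versus-control contrast as now planned. Apply the same form to the antibiotic outcomes and the exploratory outcome. Keep the analysis without Transition months as a sensitivity check. State the assumption of a common Transition effect and, if the two analyses differ materially, discuss differences in how the Transition Phase was delivered.

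The cost is one extra parameter and about one sentence of analysis text. No additional data are needed.

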4	Narrowing of prospective data collection	The protocol now includes collection of signs and symptoms prompting all urine culture orders during the Control, Transition and Intervention Phases. This allows an estimation of the proportion of cultures that are aligned with guidelines. A measure of alignment with guidelines will allow for a more precise measure of AMS compared to rate of urine culture alone. Alignment with guidelines will be used as an exploratory evaluation of the success of the trial (pre-post comparison) as well as a component of the feedback report. To balance the additional workload to LTCHs collecting this data, the protocol also limits the previously required monthly facility-level demographic data from all residents of the LTCH to only those who received a urine culture. The previous monthly facility-level demographics provided little additional value to the cross-sectional demographic data collected with the retrospective data. If some LTCHs are unable to provide signs and symptoms data, we will 1) report this finding, which will highlight an important knowledge gap, 2) remain adequately powered to evaluate the study using rate of urine culture order and 3) antibiotic prescription for UTI as previously planned.
5	Updates to feedback letter content	The protocol now calls for the feedback letter to provide a self-comparison of LTCH urine culture order rate over time, as well as an estimate of the proportion of urine culture orders that were aligned with guidelines. Previously, the protocol called for a peer-comparison of urine culture order rate between the LTCHs included in the Trial Stage, as well as comparison with historical data. The change avoids limitations of inter-home comparisons and allows for a focus on self-comparison in the spirit of continual improvement.

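### The exploratory non-aligned culture rate can fall through changed symptom recording alone, and the plan fixes no reading that would show this

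*Protocol article*

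**What the plan says.** All references are to the protocol article.

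- **Scoring (Data analysis).** "Alignment with guidelines will be estimated by comparing the signs and symptoms prompting each urine culture to meet the modified Loeb minimum criteria", separately for catheterized and non-catheterized residents.
- **Outcome (Data analysis).** "Exploratory analyses will use a similar model to evaluate the potential effect of the intervention on rate of urine cultures not aligned with guidelines". The similar model is the one for question 2a: fixed effects for phase and month, a random effect for home, Transition data left out.
- **Source of the symptoms (Appendix A, change 4).** The protocol includes "collection of signs and symptoms prompting all urine culture orders during the Control, Transition and Intervention Phases". The homes do the collecting: "To balance the additional workload to LTCHs collecting this data", other demographic reporting was cut back.
- **Teaching (Transition Phase).** Staff sessions include "a reminder of when it is and is not appropriate to test for and treat UTI in older adults". The two references cited there are the same two cited for the scoring rule.
- **Feedback (Intervention Phase).** "Feedback will also indicate the proportion of urine cultures aligned with best practice guidelines", for homes able to collect symptoms. Letters begin after the first Intervention month and repeat the guideline reminders.
- **Claim for the measure (Appendix A, change 4).** "A measure of alignment with guidelines will allow for a more precise measure of AMS compared to rate of urine culture alone". The same entry gives alignment an exploratory role in judging whether the trial succeeded, and foresees that some homes may not supply symptoms.

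**The concern.** The objective is less testing of residents who lack the minimum signs and symptoms. Among the modelled outcomes, only alignment separates those cultures from indicated ones, so readers will give it weight although it is exploratory.

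Alignment depends on what is written down as well as on what is ordered. The intervention may act on both. Staff who have been reminded of the criteria, and later see their home's aligned proportion, have reason to record a qualifying symptom that would earlier have gone unrecorded. In the non-aligned rate, a culture that was avoided and a culture that was recorded differently look the same. The trial could report less unnecessary testing when the same cultures were ordered and better documented.

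**Working it through.** **1. Does the change in recording conditions follow the phase contrast?** Table 1 gives 27 control home-months (2+2+3+3+3+4+5+5) and 29 intervention home-months (5+5+4+4+4+3+2+2). The 8 Transition months are excluded. Teaching falls in those excluded months, so every analysed control month precedes it and every analysed intervention month follows it. Letters start after the first Intervention month, so 8 of the 29 intervention home-months (one per home) precede any letter. The teaching therefore matches the phase contrast exactly, and the feedback matches it with a lag of one month.

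**2. Can the model remove it?** Month effects absorb changes common to all homes in a calendar month. The home effect absorbs stable differences between homes. A recording change that begins when a home crosses over is neither, and it goes into the phase coefficient.

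**3. How large could it be?** The plan's only effect figure is 6.5 to 5.2 per 1,000 resident days (5.2/6.5 = 0.80, a 20% reduction). It refers to the total culture rate. No figure is given for alignment of cultures; the 70.5% in the Introduction concerns prescriptions. The following is therefore illustrative.

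Let R = 6.5 (document), p = the true aligned share (assumed 0.3 to 0.6) and s = the probability that qualifying symptoms are recorded when present (assumed). R and p are held constant across phases.

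Recorded non-aligned rate = R × (1 − p × s); recorded aligned rate = R × p × s.

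- p = 0.5, s from 0.7 to 0.9: 6.5 × 0.65 = 4.225 to 6.5 × 0.55 = 3.575, an apparent fall of 15%.
- p = 0.5, s from 0.6 to 0.9: 6.5 × 0.70 = 4.55 to 3.575, a fall of 21%.
- Smallest in the range tried (p = 0.3, s from 0.8 to 0.9): 6.5 × 0.76 = 4.94 to 6.5 × 0.73 = 4.745, a fall of 4%.
- Largest (p = 0.6, s from 0.5 to 0.9): 6.5 × 0.70 = 4.55 to 6.5 × 0.46 = 2.99, a fall of 34%.

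An apparent 20% fall needs s to rise to (1 − 0.8 × (1 − p × s₀))/p, where s₀ is the control value. For p = 0.5 and s₀ = 0.6 this is (1 − 0.8 × 0.70)/0.5 = 0.88. For p = 0.3 and s₀ = 0.5 it is (1 − 0.8 × 0.85)/0.3 = 1.07, which is impossible. A fall of that size is possible under some assumptions and unreachable under others.

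**4. Which rates tell the explanations apart?** Take p = 0.5 and control s = 0.7, and let the non-aligned rate fall by 0.65 for three different reasons (rates per 1,000 resident days):

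| Situation | Non-aligned | Aligned | Total |
|---|---|---|---|
| Control, as recorded | 4.225 | 2.275 | 6.50 |
| Changed recording only | 3.575 | 2.925 | 6.50 |
| Avoided cultures only | 3.575 | 2.275 | 5.85 |
| Real shift to indicated cultures | 3.575 | 2.925 | 6.50 |

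The non-aligned column is the same in all three lower rows. The other two columns separate avoidance from the rest. They do not separate changed recording from a real shift.

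**The case against.** The strongest reply is that the safeguard already exists. Question 2a models the total culture rate as a primary question, the aligned rate is the total minus the non-aligned rate, and the Introduction plans a before/after look at the aligned proportion. Much of this stands, and it would be wrong to infer that the plan looks only at the non-aligned rate. The check is partial, however. Question 2a covers all homes, symptom data may come from fewer, and the two results are comparable only in the same homes. The before/after proportion also moves with recording. Appendix B item 1c names the aligned rate, but as something to be decreased, so it fixes no useful reading.

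The outcome is labelled exploratory, and the primary rates are counts that do not depend on symptoms. That stands in full and limits the importance of the point.

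A reader might also infer that the same untrained staff fill in the forms throughout. The article says only that homes collect the data. It does not say who records or with what instruction, and a full protocol may. Data dictionaries and templates are mentioned under retrospective collection. If used prospectively too, they would reduce the problem but not remove it while homes exposed to the teaching supply the content. The sessions are also short, 5 to 10 minutes by Appendix A, so the effect on recording may be small.

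Finally, an interpretation rule is ordinary analysis-plan content. Its absence from an article would be no finding by itself. The point rests on what the article does fix: the scoring source, the timing of teaching and feedback, and the claim made for the measure.

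**Conclusion.** The point holds for the exploratory alignment outcome. As designed, changed documentation could lower the non-aligned rate with no change in ordering, and the planned month and home effects cannot remove this. This assumes that the teaching or the feedback alters what homes report, which is plausible but not shown.

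The direction is clear and the size is not. The 4% to 34% range rests on assumed values of p and s. A reader might be tempted to say that the artefact equals the 20% effect the trial calls clinically meaningful. The document does not support that. Assuming that 20% of non-aligned cultures are relabelled yields a 20% fall by construction, and the plan's 20% is for the total rate, which recording leaves unchanged. Nor does the point reach the primary culture and prescription rates. It is a modest and inexpensive improvement to an exploratory analysis.

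**What to change.** 1. In the homes that supply symptom data, fit the planned model to the aligned rate and the total rate alongside the non-aligned rate.
2. State the reading in advance: a non-aligned fall offset by an aligned rise at an unchanged total will be reported as compatible with changed documentation as well as with a real shift, and not by itself as reduced testing.
3. Qualify the precision claim in Appendix A, change 4, by noting that symptom recording is not blinded to phase.

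The cost is two further fits on data already being collected (the total-rate fit repeats 2a in a possibly smaller set of homes), one interpretation rule and one sentence. The drawback is that a true shift towards indicated cultures with an unchanged total would be reported cautiously. That is acceptable for an exploratory outcome.
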